#### Patient timeline

The planned study duration is from 11 September 2020 to 31 October 2021. A detailed overview of the patient timeline is shown in Table 3.

**Table 3 Tab3:**
[figure not shown]
Schedule of enrolment, intervention and data collection

*Mini BESTest* Mini Balance Evaluation Systems Test, *DF* dorsiflexion, *PF* plantarflexion

#### Sample size

The study will be a pilot RCT to provide information for a subsequent larger RCT. The sample size was based on specific objectives of the study such as feasibility, acceptability and falls rather than on estimated effects of interventions. Julious recommends a minimum sample size of 12 patients per group for pilot studies [52]. Therefore, 36 people post stroke will be recruited into three groups (A, B and C). Taking into account an attrition rate of 20% and using the equation $$ N=\frac{n}{\left(1-\frac{z}{100}\right)} $$ where *n* is the sample size of 36 patients and *z* is the expected attrition rate [53], this number may increase to a total of 45 patients. For the sample size estimation of the main trial, imprecision of the standard deviation in small samples will be taken into account [54].

### Data management and data protection

Data quality will be promoted by duplicate (10MWT) or triple measurements (ankle ROM measures, utilising two different measurement approaches). Only the PI and care provider will be aware of the demographic data and have access to the pseudonymisation documents. Double data entry will be performed. Data will be verified by conducting spot checks of value ranges and field types for certain data fields, and logical checks will also be performed (e.g. the order of visits). When checking value ranges, the fields will be checked for permitted values. Field type checks concern whether the values entered fit the field definition (e.g. numerical fields). Any discrepancies found will be rectified.

For the qualitative analysis of interviews, coding will be performed by two independent coders (KT, BS). Codes will be discussed and if a consensus cannot be reached, a third researcher will provide support (FS). Post interview, the interviewer will review and ascertain that all answers have been understood correctly. Patients will be asked to provide feedback on the findings. For the report, patient quotations will be used, together with patient ID and group allocation.

German legislation states any study records and documents must be stored for a period of 10 years after the conclusion of the clinical study. Personal data will be collected, forwarded, stored and evaluated as part of this clinical study in accordance with the legal provisions of the General Data Protection Regulation (EU) 2016/679 (GDPR) and German Data Protection Act 2018 (BDSG).

### Data analyses

#### Statistical analysis

IBM SPSS Software, release 26.0 (IBM Corporation, Armonk, NY, USA) and GraphPad Prism 8, San Diego, CA, will be used for the data analyses. Statistical significance will be defined as a two-tailed *p*-value <0.05. The percentage of missing data will be recorded. Using Little’s test of missing completely at random (MCAR) [55], the data will be checked, signified by a *p*-value >0.05. An intention-to-treat analysis will be performed.

Descriptive statistics will be used for the baseline demographic variables, primary and secondary outcomes. Continuous data will be checked for normal distribution using the Shapiro-Wilk Test, Q-Q plots and histograms. Raw count (number (*N*), %) will be presented for counted (*N* females and males, *N* falls and *N* adverse events if any), compliance (types and order of home exercises, *N* of repetitions and deviations from the protocol) and nominal data (gender, recruitment, retention and adherence rates). Medians (range; 25th and 75th percentiles) will be reported for ordinal data (Mini BESTest if there are missing data, SIS); mean (95% confidence interval (CI)) will be reported for continuous data (age, Mini BESTest if data can be transformed into interval level, 10MWT, TUG, TUG_manual_, TUG_cognitive_, ankle ROM measures).

The recruitment rate (%) will be estimated by dividing the number of consenting patients by the *N* of eligible patients, multiplied by 100. The retention rate determined by dividing the *N* of patients who completed the study by the *N* of the total sample, times 100. Adherence rates will be calculated by dividing the *N* of TOT sessions (8x; 16x) performed by the patients, divided by the *N* of the scheduled (face-to-face; home-based) training sessions over the 4-week study period, times 100 [56]. The eligibility, recruitment and adherence rates will be calculated with their 95% CI according to the Wilson “score” method cited by Newcombe [57]; when the proportion is close to 0 or 1, a Poisson approximation as described by Brown and colleagues will be used [58].

Inductive statistics will detect any trends related to the intervention efficacy acting as a basis for the sample size calculation for a larger main study. The sample size estimation will be based on a power of 80%, an alpha of 5% and the standardised effect size (Cohen’s *d*). Cohen’s *d* will be calculated using the formula *d* = (mean 1−mean 2)/corrected pooled SD. The corrected pooled SD for 80% of trials will be determined using the formula $$ {SD}_{corrpool}\sqrt{\left(\frac{SD{1}^2+ SD{2}^2}{2}\right)}\ast 1.293 $$ [54]. Effect sizes will be estimated with 95% CI using an effect size calculator provided by the Centre for Evaluation and Monitoring at the University of Durham, UK [59].

Baseline group differences will be examined using the chi-square test for nominal data, Kruskal-Wallis test for ordinal data and one-way analysis of variance (ANOVA) for continuous data. If a non-normal data distribution is observed in continuous data, data transformation or non-parametrical tests will be performed, as appropriate. Kruskal-Wallis test will evaluate differences between groups and time points, followed by a Bonferroni correction for multiple comparisons. On continuous data, test assumptions for a mixed design ANOVA will be reviewed, with standard correction procedures employed appropriately. In order to evaluate the effects of the intervention on walking speed, mobility, dual-task mobility and ankle ROM, a 2-way mixed design ANOVA will be used, with “time” (*t*_1_, *t*_2_ and *t*_3_) as within-subject factor and “group” (A, B and C) as between-subject factor. If the overall group-by-time interaction is statistically significant, post hoc tests with Bonferroni correction will be applied to determine group differences in pairwise comparisons.

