#### Primary outcome and outcome measures

##### Feasibility

*Recruitment, retention and adherence rates*

The feasibility of conducting a full-scale RCT will be explored using predefined criteria, recording monthly recruitment and adherence rates to the face-to-face intervention. Using an exercise diary, adherence to the home exercise programme and any non-adherence will be recorded, including reasons (e.g. discontinuation due to lack of interest or injury). Any non-retention will also be recorded with reasons (e.g. consent withdrawn) (Fig. 1).

The criteria for feasibility success will be:
a target recruitment rate of 25% of 145 eligible patients (or 6 patients per month). The number of 145 was estimated according to information received from neurologists and clinicians practising within 30 km of the study centre, concerning the number of eligible chronic stroke patients they have treated within the previous 9 months,a target retention rate of 85%,a target minimum adherence rate of 75% for face-to-face interventions (6 practice sessions out of a maximum of 8) anda target minimum adherence rate of 75% for home-based interventions (12 practice sessions out of a maximum of 16).
b.*Compliance with the home exercise programme*

An exercise diary will be used to report compliance. Patients in groups A and B will be asked to complete an exercise diary to record type order and repetitions performed of chosen exercises. They should also explain any problems or deviations from the home exercise protocol.
c.*Adverse events and falls*

Falls are considered a relevant outcome from a mobility and balance intervention study because of the associated injury risk. Any adverse events and side effects will be systematically recorded and evaluated using a formal log including the type of adverse event, dates, severity, causality differentiated into serious/non-serious, actions to restore or improve the patient’s wellbeing and outcome of the event. A falls log will be provided to patients, which will be collected at *t*_2_ and *t*_3_, in addition to the number of and reasons for falls within prior 6 months. Study-related adverse events such as training-related injuries will be treated and paid for. Severe adverse events will lead to early study termination.
d.*Acceptability of the intervention*

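### The Wilson interval for adherence treats repeated sessions from the same patient as independent, so it overstates the precision of a primary feasibility outcome

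*Protocol article*

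**What the plan says.** Under Statistical analysis, the protocol article builds the adherence rate from the number "of TOT sessions (8x; 16x) performed by the patients, divided by the" number "of the scheduled (face-to-face; home-based) training sessions over the 4-week study period, times 100". The counts 8 and 16 are the sessions each patient is scheduled to have. The interval follows in the same section: "The eligibility, recruitment and adherence rates will be calculated with their 95% CI according to the Wilson" score method, with a Poisson approximation when a proportion is close to 0 or 1. Adherence thus shares one method with eligibility and recruitment, for which each patient counts once.

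Under Feasibility, the list introduced by "The criteria for feasibility success will be" has four entries, two of which concern adherence: a "target minimum adherence rate of 75% for face-to-face interventions (6 practice sessions out of a maximum of 8") and a "target minimum adherence rate of 75% for home-based interventions (12 practice sessions out of a maximum of 16"). Feasibility is the primary outcome. Table 1 adds that adherence will be reported as a median (range) of times per week and as a percentage with a 95% confidence interval.

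**The concern.** The Wilson interval takes its width from the number of independent binary observations. For eligibility and recruitment that number is a count of people. For adherence as defined here it is a count of sessions, with 8 or 16 from each person. A patient who loses interest or is injured misses a run of sessions together. The article expects such cases, since it records discontinuation with reasons and allows for 20% attrition. Nothing in the article allows for this correlation.

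At stake is the only stated measure of uncertainty for two of the four success criteria. An interval that is too short makes the result look better established, relative to 75%, than about 24 patients can support, and that picture would inform the decision on a full-scale trial.

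**Working it through.** **Inputs from the article.** Sample size: "Therefore, 36 people post stroke will be recruited into three groups (A, B and C"), allocated 1:1:1, so 12 per group. Group C has no training sessions, so 24 patients contribute. Sessions per patient: m = 8 face-to-face, m = 16 home-based.

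**The article's own figures.** 6/8 = 12/16 = 0.75, and 36/(1 - 0.20) = 45; both reproduce. No interval width for adherence is stated.

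**Step 1: the interval as written.** 24 × 8 = 192 and 24 × 16 = 384 sessions; 75% is 144 and 288. The Wilson limits are [p + z²/(2n) ± z√(p(1-p)/n + z²/(4n²))] / (1 + z²/n), with z = 1.96.
- n = 192: (0.7600 ± 0.0621)/1.0200 gives 68.4-80.6%.
- n = 384: (0.7550 ± 0.0436)/1.0100 gives 70.4-79.1%.

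**Step 2: allow for clustering.** Design effect DE = 1 + (m - 1) × ICC; effective n = 24m/DE; Wilson is then applied to the effective n. The ICC is assumed, over a range.

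| Sessions | ICC | DE | Effective n | 95% CI at 75% | Width relative to step 1 |
|---|---|---|---|---|---|
| Face-to-face | 0.1 | 1.7 | 113 | 66.3-82.1% | 1.30 |
| Face-to-face | 0.3 | 3.1 | 62 | 63.0-84.1% | 1.74 |
| Face-to-face | 0.5 | 4.5 | 43 | 60.3-85.5% | 2.07 |
| Home | 0.1 | 2.5 | 154 | 67.6-81.2% | 1.57 |
| Home | 0.3 | 5.5 | 70 | 63.7-83.7% | 2.31 |
| Home | 0.5 | 8.5 | 45 | 60.8-85.3% | 2.84 |

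**Step 3: actual coverage.** Beta-binomial simulation with 24 patients and a true rate of 75%. At ICC 0.1, 0.3 and 0.5 the session-level Wilson interval contains 75% in about 86%, 72% and 63% of trials (face-to-face) and 78%, 59% and 49% (home); separate simulation runs differ by about one point. The lower limit lies above 75%, nominally a 2.5% event, in about 6.5%, 13.7% and 18.5% (face-to-face) and 10.5%, 21.0% and 26.1% (home). A patient-level t interval covers about 94-95% throughout.

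**Step 4: is such an ICC plausible?** As an illustration, suppose the planned 20% attrition falls within the training period, dropouts stay in the denominator and the overall rate is 75%. If dropouts attend a fraction a and the others b = (0.75 - 0.2a)/0.8, then ICC ≈ 0.2 × 0.8 × (b - a)²/(0.75 × 0.25).
- a = 0.5: b = 0.8125, ICC ≈ 0.08.
- a = 0.3: b = 0.8625, ICC ≈ 0.27.
- a = 0: b = 0.9375, ICC ≈ 0.75.

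The range used in steps 2 and 3 is therefore reasonable, though the article does not supply it.

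**Step 5: the point estimate.** Every patient has the same m, so the mean of the per-patient fractions equals total sessions performed over total scheduled. A patient-level analysis leaves the estimate as it is and changes only the interval.

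**The case against.** The strongest reply is that the interval decides nothing. The 75% figures are targets, no confidence limit or test is attached to them, and the article calls all its results preliminary. This stands. A reader might infer that the narrow interval could turn a failed criterion into a met one, but the article does not support that: the point estimate is the same with or without clustering.

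A second reply is that the article never says sessions are pooled. It lists adherence among nominal data beside per-patient rates, and it writes the targets as 6 of 8 and 12 of 16. If the rate were the share of patients reaching those counts, Wilson on 24 patients would be valid (18/24: 55.1-88.0%). This stands in part. The formula under Statistical analysis, however, divides sessions by sessions and does not define such a share, so the session-level reading is the plain one.

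A third reply is that the size depends on an ICC nobody has given. This also stands. At ICC 0.1 the correct face-to-face interval is only 1.30 times as wide. Nor should one conclude that the data are worth only 24 observations: that needs an ICC of 1, and at 0.3 the effective numbers are about 62 and 70. Finally, the median and range in Table 1 would reveal extreme non-attenders, but they do not correct the interval.

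**Conclusion.** The stated interval does not suit the stated rate. The direction of the error is certain for any positive within-patient correlation; its size is conditional on the ICC. For assumed ICCs of 0.1 to 0.5, coverage falls from the nominal 95% to between about 86% and 63% for face-to-face sessions and between about 78% and 49% for home sessions. These figures assume 24 contributing patients, the full 8 or 16 scheduled sessions each, and a true rate of 75%. Recruiting up to 45 (30 in groups A and B) would shorten all the intervals but leave the design effects as they are.

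The consequence is false precision around two of the four success criteria, not a changed pass or fail. It is a moderate point, worth correcting before analysis because the correction is cheap.

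**What to change.** In Statistical analysis, restrict the Wilson interval (and its Poisson variant, which also assumes independence) to rates with one observation per patient, such as eligibility and recruitment. For adherence, state that the patient is the unit, and report mean per-patient adherence for face-to-face and for home-based training, each with a patient-level t, bootstrap or cluster-robust 95% interval. The 75% targets stay as they are.

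The share of group A and B patients reaching 6/8 and 12/16, with a Wilson interval on patients, may be added as a descriptive supplement. It should not replace the criterion, because it is a different quantity for which the article sets no target.

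The cost is a change of wording and a wider interval. No new data are needed.

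### The SD multiplier of 1.293, labelled as holding for 80% of trials, fits 9 degrees of freedom rather than the 22 of a pooled SD from two groups of 12, and would oversize the main trial by about 24%

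*Protocol article*

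**What the plan says.** The Sample size section of the protocol article cites "a minimum sample size of 12 patients per group for pilot studies", which gives 36 patients in three groups, or up to 45 after a 20% allowance for attrition. For sizing the main trial it promises that "imprecision of the standard deviation in small samples will be taken into account".

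The Statistical analysis section carries this out. "The sample size estimation will be based on a power of 80%, an alpha of 5% and the standardised effect size", and d is defined as the difference of two means over a corrected pooled SD. On that SD it says "The corrected pooled SD for 80% of trials will be determined using the formula". The formula takes the square root of the average of the two group variances and multiplies it by 1.293. No degrees of freedom are given for the constant. The next sentence says that effect sizes with 95% CI will come from an external effect size calculator. It does not say which SD is entered there.

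**The concern.** A small-sample SD correction depends on how many degrees of freedom stand behind the SD. The article prints one constant without them, so the constant has to agree with the article's own group sizes and its own 80% label. It does not: 1.293 is larger than a pooled SD from two groups of the planned size needs at that level.

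The sample size of the main trial is a stated product of this pilot (Abstract, key secondary outcome, Statistical analysis, and Study limitations and strengths). It scales with the square of the multiplier, so an error in the constant passes directly into the number of patients sought later. A second question follows from the layout of the section. The inflated SD is written into the definition of Cohen's d, and the article then speaks of effect sizes with confidence intervals without saying whether the same d is meant.

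**Working it through.** **Inputs.** From Statistical analysis: the multiplier 1.293, the 80% label, a pooled SD from two groups, 80% power, 5% alpha, two-tailed. From Sample size: 12 per group, three groups, 36 in total, up to 45 with attrition. Assumed for illustration: an observed, uncorrected d of 0.5, since the article gives no effect size.

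**Step 1: reproduce the plan's figure.** The one-sided 80% upper limit for an SD multiplies the estimate by f(df) = sqrt(df / chi-square 20th percentile on df). At 9 df this is sqrt(9 / 5.380) = 1.2934, which agrees with the constant to three decimals. In a search over 2 to 79 df, no other value gave 1.293 on the SD scale at the 80% level.

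**Step 2: put in the planned sizes.** The excess in N is (1.293 / f)² − 1. The coverage of 1.293 is the probability that chi-square on df exceeds df / 1.293².

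| SD taken from | df | f at 80% | Excess in N with 1.293 | Coverage of 1.293 |
|---|---|---|---|---|
| One sample of 10 | 9 | 1.293 | none | 80.0% |
| One group of 12 | 11 | 1.255 | 6% | 83.2% |
| Two groups of 10 | 18 | 1.183 | 19% | 90.4% |
| Two groups of 12 | 22 | 1.161 | 24% | 92.9% |
| Two groups of 15 | 28 | 1.139 | 29% | 95.3% |
| Three groups of 12 | 33 | 1.126 | 32% | 96.7% |

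For the planned case: sqrt(22 / 16.314) = 1.161, and (1.293 / 1.161)² = 1.24. None of the group sizes that follow from the Sample size section, pooled over two or three arms or taken singly, gives 1.293.

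**Step 3: patients.** Two-sample t-test, two-sided 5%, 80% power, observed d = 0.5:
- no correction: 64 per group
- factor 1.161, d = 0.5 / 1.161 = 0.431: 86 per group
- factor 1.293, d = 0.5 / 1.293 = 0.387: 106 per group

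The difference is 20 per group. The normal approximation gives 63, 85 and 105. The ratio of about 1.24 hardly depends on d: by the same approximation it is 236 against 292 at d = 0.3, and 34 against 42 at d = 0.8.

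**Step 4: the effect on d.**
- 1.293 against no correction: 1 − 1/1.293 = 22.7% smaller
- 1.161 against no correction: 1 − 1/1.161 = 13.9% smaller
- 1.293 against 1.161: 1 − 1.161/1.293 = 10.2% smaller

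Only the last figure is due to the wrong degrees of freedom.

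**The case against.** **The constant rests on a source that is not at hand.** The article cites a reference for 1.293, and the reading as a one-sided chi-square limit is an inference from the 80% label. That is fair, and what the authors intended cannot be settled here. But the agreement at 9 df is to three decimals, and other readings do worse. A 95% limit would give 1.293 at 27 df, close to two groups of 15, but the article says 80%. On the variance scale an 80% limit gives 1.297 at 28 df and 1.290 at 29 df, but the formula applies the factor to the SD. The mismatch with two groups of 12 stands.

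**The error is conservative and lies downstream.** This stands. The later trial would be too large, not underpowered. The pilot's feasibility outcome and its own sample size are unaffected, and the calculation is made once the data are in and the real degrees of freedom are known.

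**Other uncertainty is larger.** This also stands. The observed mean difference from 12 per group is imprecise: at an assumed d of 0.5 its standard error is about sqrt(2/12 + 0.25/48) = 0.41. A 24% change in N is small beside that. It is still a systematic excess that costs nothing to remove.

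**Stronger readings that the article does not support.** A reader might infer that the published pilot effect sizes will be shrunk by 23%. The article brings in the corrected SD for sizing the main trial and describes the effect sizes with 95% CI in a separate sentence, with a separate tool, so whether the inflated SD enters there is unclear. The 22.7% also compares with no correction at all, and 13.9% would remain with the right factor. A reader might also infer that the plain average of two variances is spoiled by unequal arms. Allocation is 1:1:1, and no material effect of imbalance has been shown. Finally, the 93% is coverage of the SD at 22 df. It is not assurance of the main trial's power.

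**Conclusion.** The multiplier is wrong for the design that the article describes. At its stated 80% level, 1.293 belongs to 9 df, while a pooled SD from two groups of 12 has 22 df and needs 1.161. Used as written, it covers about 93% of trials instead of 80% and makes the main trial about 24% too large, with a range of 19% to 32% over 18 to 33 df. The d used for sizing is about 10% smaller than the correction at 22 df would make it.

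This rests on reading the 80% label as a one-sided upper confidence limit for an SD, on normally distributed data, and on 12 analysed patients per group. The patient numbers also assume an observed d of 0.5; the percentages do not. The error is conservative and confined to the later trial's size. Which SD underlies the effect sizes reported with 95% CI is an ambiguity to be resolved, not a demonstrated bias.

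**What to change.** In Statistical analysis, replace 1.293 by sqrt(df / chi-square 20th percentile on df), evaluated at the actual residual degrees of freedom of the pooled SD. Give 1.161 as the value for two groups of 12. If the SD is to be pooled over all three arms, say so; the value is then 1.126 for three groups of 12.

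Add one sentence stating that the inflated SD is used only in the main-trial sample-size calculation, and that the pilot effect size with its 95% CI uses the ordinary pooled SD.

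The cost is one constant and one sentence. Nothing changes in recruitment, assessment or data collection. The change should be in place before the main trial is sized.

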### Study design and location

The supporting CONSORT checklist for this study is available as additional information; see Additional file 1. This will be a prospective randomised controlled pilot trial in chronic stroke patients comprising two parallel intervention groups and a control group. The primary outcome will be feasibility assessed by recruitment, retention and adherence rates, compliance, adverse events, falls and the acceptability of the intervention. Block randomisation will use permuted blocks of 3 and 6 and 1:1:1 allocation. A CONSORT flow diagram is shown in Fig. 1. The study location will be a physiotherapy practice in rural Germany, chosen because the home-based intervention has been designed for stroke patients at the chronic stage who have regained at least a minimum level of mobility.

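### A normality check on about 12 patients per group can change the analysis of a continuous outcome, and the only rank test named does not address the group-by-time interaction or the repeated visits

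*Protocol article*

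**What the plan says.** All of this is in the Protocol article, mostly under Statistical analysis.

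- **The check:** "Continuous data will be checked for normal distribution using the Shapiro-Wilk Test, Q-Q plots and histograms". The text gives no cut-off. It does not say whether raw values or residuals are checked, or whether this is done per group and visit or pooled.
- **The consequence:** "If a non-normal data distribution is observed in continuous data, data transformation or non-parametrical tests will be performed, as appropriate". No rule separates the two options.
- **The rank test:** the next sentence reads "Kruskal-Wallis test will evaluate differences between groups and time points", followed by a Bonferroni correction.
- **The parametric model:** a two-way mixed ANOVA with three visits and three groups is planned for walking speed, mobility, dual-task mobility and ankle range of motion. Its assumptions are to be reviewed and standard corrections applied. Pairwise tests follow only if the group-by-time interaction is significant.
- **The Mini BESTest:** it is treated as continuous when it can be converted to interval scores. Under Key secondary outcome, its preliminary changes are to size the main trial.
- **Size:** the Sample size section relies on this statement: "Julious recommends a minimum sample size of 12 patients per group for pilot studies". After allowing for attrition, "this number may increase to a total of 45 patients".

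**The concern.** Under these rules the data help to decide which analysis an outcome receives. A transformation keeps the mixed ANOVA and its interaction, though on another scale. A move to Kruskal-Wallis does not keep the interaction. Comparing groups at one visit asks whether levels differ then, whereas the interaction asks whether the groups changed differently. Comparing visits with Kruskal-Wallis treats three measurements on one patient as if they came from three patients.

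Two outcomes of the same kind could therefore be analysed in different ways and answer different questions. The rule also reaches the interval-scored Mini BESTest, which matters more than the rest because the main trial is to be sized on it.

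**Working it through.** **Inputs from the protocol.** Three groups, 1:1:1, 12 per group, three visits, two-sided 5%. The protocol's own inflation reproduces: 36 / (1 − 0.20) = 45, or 15 per group.

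**Assumed inputs.** The protocol gives no within-patient correlation, skewness or effect size. The simulations use equal correlation between visits, with 2,000 runs for the normality check (correlation 0.7) and 4,000 for the test comparisons.

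**1. False flags when the data are truly normal (12 per group).**

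- Any of nine group-by-visit cells, if independent: 1 − 0.95⁹ = 37%. Simulated with correlated visits: about 34 to 35%.
- Residuals pooled over groups, any of three visits, if independent: 1 − 0.95³ = 14%. Simulated: about 14%.
- One given cell: 5%.

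With 15 per group these rates are much the same (35%, 13% and 5%).

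**2. Detection of real skewness (log-normal data, 12 per group).** Share of trials flagged by Shapiro-Wilk:

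| SD on log scale | One given cell | Any of nine cells | Pooled residuals, any visit |
|---|---|---|---|
| 0.25 | 11% | 61% | 53% |
| 0.4 | 21% | 83% | 85% |
| 0.5 | 30% | 93% | 94% |
| 0.7 | 48% | 99% | 99% |

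False flags and detection must be compared under the same unit. Per cell, the check separates normal from skewed data poorly (5% against 11 to 48%). On pooled residuals it separates them well once the skew is marked (14% against 85% or more from log-SD 0.4).

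**3. Kruskal-Wallis between groups answers another question.** Let group A differ by a constant 0.8 SD at all three visits, so that there is no interaction. Kruskal-Wallis at *t*₂ rejects in about 43 to 46% of trials. The mixed-ANOVA interaction rejects in about 5%, as it should.

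**4. Kruskal-Wallis across visits ignores the pairing (one group of 12).** The Friedman test, which respects the pairing, is the comparator. The last two columns are power for a 0.8 SD change at *t*₂ and *t*₃.

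| Correlation | KW, null | Friedman, null | KW, power | Friedman, power |
|---|---|---|---|---|
| 0.5 | 0.6% | 5.7% | 38% | 65% |
| 0.7 | 0.1% | 5.7% | 36% | 86% |
| 0.85 | 0.0% | 5.6% | 36% | 99% |

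**5. Power against the test that is planned.** The effect is 0.8 SD in A and 0.4 SD in B at *t*₂ and *t*₃, with 12 per group.

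| Correlation | Mixed-ANOVA interaction | KW between groups at *t*₂ | KW on change *t*₂ − *t*₁ |
|---|---|---|---|
| 0.5 | 37% | 34% | 34% |
| 0.7 | 60% | 34% | 53% |
| 0.85 | 91% | 34% | 84% |

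With 0.8 SD in both A and B, the interaction has about 50%, 75% and 92% power at correlations 0.5, 0.7 and 0.8. Kruskal-Wallis at *t*₂ stays at about 45%.

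**The case against.** **Scope.** The conditional sentence directly follows the one on baseline comparisons. The sentence after the Kruskal-Wallis one turns to continuous data, which suggests that Kruskal-Wallis is meant for ordinal outcomes. The mixed ANOVA is then stated without condition. This stands as an ambiguity. The conditional sentence still speaks of continuous data generally, and no other rank method is named for it. Even on the narrow reading, Kruskal-Wallis across visits is unsuitable for ordinal repeated measures.

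**Stronger readings.** A reader might infer three things that the document does not support.

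- *That the analysis is picked by noise.* Transformation is offered first and keeps the mixed ANOVA. Plots are used as well as Shapiro-Wilk, and the unit of the check is not stated. Chance dominates only for per-cell checks or mild skew.
- *That power is roughly halved.* A contrast of 44% with 88 to 90% arises if Kruskal-Wallis is set against change-score ANOVA or ANCOVA at correlation 0.8. Neither of those is the planned test, and the correlation is assumed. Against the planned interaction the gap runs from a few points to large.
- *That transforming timed tests, walking speed or range of motion would distort the main-trial sample size.* That calculation rests on the Mini BESTest, and the Cohen's *d* formula is not tied to whichever test is chosen.

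**Level of detail.** Cut-offs and exact fallback tests are often left to an analysis plan, which is not shown. That is fair as regards omissions. The point here is a rule that the article does state, and a fallback test that it does name.

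**Conclusion.** The point holds, with limited reach. The section lets a normality check choose between the mixed ANOVA, a transformed version and a non-parametric test. The only rank test it names does not test the interaction and is unsuitable across visits. These last two faults do not depend on how well the normality check performs.

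Whether the rule governs the efficacy outcomes is the natural reading but not certain. If it does, a move to ranks changes the question. The loss of power is small at a within-patient correlation of 0.5 and large at 0.7 to 0.85. The false-flag rate is about 34% or about 14%, depending on a unit that the document leaves open.

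These figures rest on assumed correlations, effects and log-normal skew. The outcomes are secondary and exploratory, feasibility is primary, and the sample was not sized on treatment effects, so the consequence is modest. The correction is still worth making because it is cheap and covers the outcome that sizes the main trial.

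**What to change.** 1. For each continuous outcome, including the interval-scored Mini BESTest, fix one scale and one group model that uses baseline before outcome data are unblinded. Keep both whatever the normality result.
2. Drop the normality check as a switch between analyses. Use residual plots from the fitted model only as a check.
3. Replace Kruskal-Wallis across time points with a sensitivity analysis suited to repeated measures, such as ranks of change from baseline, rank ANCOVA or a bootstrap interval.
4. State which outcomes each rule covers, so that baseline comparisons, ordinal outcomes and efficacy outcomes are no longer run together.

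The cost is a few sentences in the analysis section, with no extra patients or visits. The one downside is that any outcome fixed on a log scale is reported as a ratio rather than a difference.
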